### Procedure

#### Initial assessment

Following referral, the caregivers of potential child and adolescent participants will be briefly screened over the phone to determine suitability for baseline assessment using a checklist developed for this study. Information collected as part of this assessment will include psychiatric diagnoses and psychiatric symptoms - to identify anxiety as the primary presenting problem and consider differential diagnoses - as well as current and previous treatment including medication (type, dosage, period of pharmacological treatment) in accordance with the aforementioned inclusion and exclusion criteria. If deemed suitable at this point, they will be sent an information pack about the study including consent forms, and a battery of questionnaires to be completed by both the child/adolescent and caregiver as part of the baseline assessment. All assessment tools employed have demonstrated reliability and validity (described in detail below). To complete the baseline assessment the child/adolescent and parent will attend CHW to undertake a face-to-face diagnostic interview to determine the presence of an anxiety disorder using the Anxiety Disorders Interview Schedule for DSM-IV [ADIS-IV] (Silverman & Albano, 1996). ADIS-IV interviews of both parent/caregiver and child/adolescent which will be conducted separately by psychologists trained in the administration of the instrument. All interviews will be recorded for reliability purposes. The researchers conducting baseline assessments will be blinded to the treatment type to reduce potential.

#### Randomization

Following baseline assessment, eligible participants and their caregivers will be randomized to one of three conditions - ACT, CBT or a waitlist control group - for a period of 10 weeks (described in detail below). Each group will comprise up to eight children/adolescents as well as their caregivers. The researchers involved in this study are six registered psychologists, all trained in ACT and CBT. This will be a block randomized controlled trial, with the participant serving as the unit of randomization. Randomization will be undertaken via a publically available random assignment software application, ‘Graphpad’ [http://www.graphpad.com/quickcalcs/].

#### Follow-up assessment

Follow-up repeated measures assessment will be completed immediately post-treatment - or after 10 weeks for the control group - and three months post-treatment for both intervention groups. Following completion of the 10-week post assessment, the control group will complete a program of 10 × 1.5 hour sessions of CBT. Although it will not be possible to ensure the researchers conducting post-intervention and follow-up assessments will be blinded to the treatment type, to reduce potential bias these interviews will be recorded for reliability purposes and reviewed and re-rated by an independent assessor - a psychologist within the Department of Psychological Medicine with training in the use of the ADIS-IV - blind to the diagnosis obtained. Participants will also be assessed on the uptake of pharmacotherapy throughout the course of the trial at follow-up.

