For the primary aim of the trial, relating to efficacy of the intervention, the primary outcome measures will be whether the participant meets criteria for one or more DSM-IV anxiety disorders and/or clinically significant changes in severity scores on the ADIS-IV, CBCL or MASC assessments. Clinically significant change will be defined as a change in score that places the participant within a different severity range on the relevant assessment. For the ADIS-IV, this will be a shift in interference ratings between ‘Very severe’ (8), ‘Severe’ (6 to 7), ‘Moderate’ (4 to 5), ‘Mild’ (1 to 3) or ‘Absent’ (0) ranges [45]. For the CBCL, this will be represented by a change in t-scores among the ‘Clinical’ (≥69); ‘Borderline clinical’ (56 to 69) and ‘Normal’ (≤55) ranges [41]. For the MASC, in accordance with March [37], this will be a shift in t-score between the ‘Severe’ (≥70); ‘Moderate’ (56 to 69) and ‘Non-clinical’ (≤55) ranges. Secondary outcome measures will include anxiety symptoms; (depression symptoms; and quality of life and self-efficacy (Table 1).

**Table 1 T1:** Primary and secondary outcome measures as they relate to the efficacy aim

**Intervention efficacy outcome measures**	**Assessment tool/measured factor**
*Primary measures*	
DSM-IV Anxiety disorder	ADIS-IV
Clinically significant change in anxiety severity	ADIS-IV, MASC, CBCL
*Secondary measures*	
Depression symptoms	CDI, CBCL
Quality of life and self-efficacy	CALIS-C
Demographic factors	FAD, age, sex

ADIS-IV, Anxiety Disorders Interview Schedule; CALIS-C, Children’s Anxiety Life Interference Scale - Child Form; CBCL, Child Behavior Checklist - Parent Form; CDI, Child Depression Inventory; DSM-IV, Diagnostic and Statistical Manual of Mental Disorders; FAD, Family Assessment Device; MASC, Multidimensional Anxiety Scale for Children.

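### The ADIS-IV re-rater is stated to be blind to the diagnosis but not to treatment arm, so the safeguard as written does not address the bias it is meant to reduce

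*Protocol article*

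**What the plan says.** The Follow-up assessment section accepts that "it will not be possible to ensure the researchers conducting post-intervention and follow-up assessments will be blinded to the treatment type". The same sentence gives the remedy: "to reduce potential bias these interviews will be recorded for reliability purposes and reviewed and re-rated by an independent assessor". That assessor is "a psychologist within the Department of Psychological Medicine" and is "with training in the use of the ADIS-IV - blind to the diagnosis obtained".

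Masking to treatment is named once, under Initial assessment: "The researchers conducting baseline assessments will be blinded to the treatment type". Allocation comes later, since under Randomization "Following baseline assessment, eligible participants and their caregivers will be randomized to one of three conditions".

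The ADIS-IV matters because the section on primary outcome measures defines the primary outcome as "whether the participant meets criteria for one or more DSM-IV anxiety disorders and/or clinically significant changes in severity scores on the ADIS-IV, CBCL or MASC". The ADIS-IV therefore supplies the diagnosis and one of the three severity-change measures. The same section describes the MASC as self-report and the CBCL as a parent form.

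**The concern.** The difficulty the article names is that the person rating the outcome may know the arm. The masking it specifies is to something else, namely the diagnosis already recorded. A re-rater who has not seen the first diagnosis but knows the arm can still be influenced by expectation, in the same direction as the interviewer.

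The ADIS-IV is the only assessor-rated instrument among the primary measures, and so the only one for which a masked assessor can be arranged. Children and parents completing the MASC and CBCL know whether they are in therapy or waiting, which is unavoidable in this design. In its Background the article itself criticizes earlier studies for relying on self-reports and on unblinded informants. A masked ADIS-IV rating is the trial's available protection against that criticism, so its wording should be exact.

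**Working it through.** The article gives no figure to reproduce. The check sets the statements side by side.

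| Step | What the article states | What it protects |
|---|---|---|
| Baseline interview (Initial assessment) | Assessor masked to treatment type | Eligibility decisions and pre-treatment scores; not outcome ratings, since allocation follows baseline |
| Post-treatment and follow-up interview (Follow-up assessment) | Masking to treatment type cannot be ensured | Nothing assured |
| Re-rating of the recording (Follow-up assessment) | Masked to the diagnosis obtained; arm not mentioned | Independence of the second rating from the first |
| Value used in the analysis | Not stated | Unknown |

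1. **Purpose against means.** The stated aim of the re-rating is to reduce bias, and the bias in question comes from knowing the treatment. Masking to the first diagnosis removes anchoring on the first rater. It does not remove knowledge of arm.
2. **Whether arm masking appears elsewhere.** It is named at baseline only. No other section states it for outcome ratings, and nothing is said about keeping mention of therapy out of the recorded interviews.
3. **Whether independence fills the gap.** Under Treatment fidelity, the fidelity assessor is specified as someone not involved in the treatment groups. The ADIS-IV re-rater is called independent and placed in the same department, without that specification.
4. **Whether the re-rating counts.** Even a fully masked re-rating protects the outcome only if it is the value analysed. Neither Follow-up assessment nor Statistical analysis says so.

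**Illustration of sensitivity only.** Suppose there is no true difference, the arm-aware rating is the one analysed, and knowledge of arm shifts a continuous rating by *b* standard deviations in one arm. With *n* per arm, the standard error is √(2/n), and the chance of P < 0.05 (two-sided) is

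Φ(b/√(2/n) − 1.96) + Φ(−b/√(2/n) − 1.96).

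For *n* = 50 (150 participants over three equal arms) and *b* = 0.2, √(2/50) = 0.2, so the chance is Φ(−0.96) + Φ(−2.96) ≈ 0.17.

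| Assumed shift *b* | 30 per arm | 50 per arm |
|---|---|---|
| 0.1 SD | 7% | 8% |
| 0.2 SD | 12% | 17% |
| 0.3 SD | 21% | 32% |
| 0.5 SD | 49% | 71% |

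The nominal rate is 5%. The shifts are assumptions and appear nowhere in the document. The table shows that modest shifts would matter if they occurred, not that they will.

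**The case against.** The strongest reply is that this is loose wording in a condensed article. The sentence opens with masking to treatment type and offers the re-rating as the answer, so the authors may well intend the re-rater to be masked to arm. File coding and similar detail can fairly be left to the full protocol, and the choice of rating to the analysis plan. This stands in part: the text is silent, and it does not say that the re-rater knows the arm. It does not dispose of the point. The article states what the re-rater is masked to, and that item does not answer the problem it has just raised.

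A reader might also infer more than the text supports:

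- **That the unmasked interviewer's rating is the outcome**, because reliability is mentioned. That phrase attaches to the recording, as it also does under Initial assessment. The declared aim of the step is to reduce bias, and which rating is analysed is left open.
- **That masking at baseline is worthless.** It cannot protect outcome ratings, but it does protect eligibility decisions and the pre-treatment scores from which change is measured.
- **That the whole primary outcome is open to rater bias.** Only its ADIS-IV components are rated by an assessor.
- **That the article's attention to allegiance shows the re-rater to be partial.** The allegiance question under Treatment fidelity concerns the psychologists delivering therapy, and its association with outcome is already to be examined.

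**Conclusion.** The point holds in a limited form. The article acknowledges that ADIS-IV interviewers may know the treatment after baseline, and it answers with a re-rating whose stated masking is to the diagnosis alone. Followed as written, this gives an independent second rating. It does not protect ADIS-IV diagnosis or ADIS-IV severity change from bias due to knowledge of arm. The silence on which rating is analysed adds to this, since a masked rating that is not used protects nothing.

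The document does not support the claim that the re-rater is unmasked, or that any bias has a particular size or direction. The percentages above rest on assumed shifts and on the arm-aware rating being the one analysed, so they carry no weight in this conclusion. This is a cheap improvement to a safeguard already in place, not a demonstrated flaw in the results to come.

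**What to change.** Amend the Follow-up assessment section to state that:

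- the re-rater is masked to treatment arm and, where feasible, to time point. A three-month recording can come only from an active arm, because three-month assessment is described for the two intervention groups alone;
- the re-rater treats no trial group, matching the condition already set for the fidelity assessor;
- recordings carry coded names, and interviewees are asked not to mention their therapy;
- the masked rating is the ADIS-IV value in the primary analysis, with the interviewer's rating kept for agreement and sensitivity analysis.

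Severity change also needs a baseline value, so the text should say which rating supplies it.

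If arm masking is already intended, one sentence settles that part. No new assessor or recording is needed, and the trial status is still recruiting. The cost is coding the files and some delay before the primary rating is available. Masking of this kind will not be perfect, since an interviewee may still reveal the therapy.

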#### Outcome measures

### Primary outcome measures

*Anxiety Disorders Interview Schedule (ADIS-IV)*[32]*.* The ADIS-IV is a structured diagnostic interview that assesses for a range of DSM-IV disorders typically first diagnosed in childhood or adolescence [33] from the perspective of both child (ADIS-C) and parent (ADIS-P) [34]. The ADIS-C and ADIS-P demonstrate good-to-excellent clinician inter-rater agreement, diagnostic reliability and test-retest reliability [35,36].

*Multidimensional Anxiety Scale for Children (MASC)*[37]*.* The MASC is a 39-item self-report inventory of anxiety symptoms. It assesses four factors of anxiety including physiological symptoms, avoidance, social and separation anxiety [34,38]. Research has shown the MASC exhibits acceptable convergent and divergent validity, moderate-to-strong internal reliability, and adequate test-retest and discriminate validity [34,39,40].

*Child Behavior Checklist - Parent Form (CBCL)*[41]*.* The CBCL is a widely utilized standardized measure of children’s and adolescents’ (aged 5 to 18 years) emotional and behavioral functioning as well as social competence [42]. The social competence scales examine the child’s adaptive functioning including their activities, and social and school performance [42]. Behavioral and emotional functioning is assessed by 118 items, which describe an array of problems that children might experience [42,43]. Validity and reliability data were obtained in a sample of over 5,000 children and were found to be moderate-to-high and high, respectively [44].

For the primary aim of the trial, relating to efficacy of the intervention, the primary outcome measures will be whether the participant meets criteria for one or more DSM-IV anxiety disorders and/or clinically significant changes in severity scores on the ADIS-IV, CBCL or MASC assessments. Clinically significant change will be defined as a change in score that places the participant within a different severity range on the relevant assessment. For the ADIS-IV, this will be a shift in interference ratings between ‘Very severe’ (8), ‘Severe’ (6 to 7), ‘Moderate’ (4 to 5), ‘Mild’ (1 to 3) or ‘Absent’ (0) ranges [45]. For the CBCL, this will be represented by a change in t-scores among the ‘Clinical’ (≥69); ‘Borderline clinical’ (56 to 69) and ‘Normal’ (≤55) ranges [41]. For the MASC, in accordance with March [37], this will be a shift in t-score between the ‘Severe’ (≥70); ‘Moderate’ (56 to 69) and ‘Non-clinical’ (≤55) ranges. Secondary outcome measures will include anxiety symptoms; (depression symptoms; and quality of life and self-efficacy (Table 1).

**Table 1 T1:** Primary and secondary outcome measures as they relate to the efficacy aim

**Intervention efficacy outcome measures**	**Assessment tool/measured factor**
*Primary measures*	
DSM-IV Anxiety disorder	ADIS-IV
Clinically significant change in anxiety severity	ADIS-IV, MASC, CBCL
*Secondary measures*	
Depression symptoms	CDI, CBCL
Quality of life and self-efficacy	CALIS-C
Demographic factors	FAD, age, sex

ADIS-IV, Anxiety Disorders Interview Schedule; CALIS-C, Children’s Anxiety Life Interference Scale - Child Form; CBCL, Child Behavior Checklist - Parent Form; CDI, Child Depression Inventory; DSM-IV, Diagnostic and Statistical Manual of Mental Disorders; FAD, Family Assessment Device; MASC, Multidimensional Anxiety Scale for Children.

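### Clinically significant change is defined by crossing a severity band, with no minimum size and no direction, so under plausible assumptions measurement error alone produces a sizeable share of changers in every arm

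*Protocol article*

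**What the plan says.** The Primary outcome measures section makes diagnostic status the first element of the primary outcome and then adds "and/or clinically significant changes in severity scores on the ADIS-IV, CBCL or MASC assessments". The rule for such a change is: "Clinically significant change will be defined as a change in score that places the participant within a different severity range on the relevant assessment".

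The ranges are printed for each instrument:

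- ADIS-IV: "a shift in interference ratings between ‘Very severe’ (8), ‘Severe’ (6 to 7), ‘Moderate’ (4 to 5), ‘Mild’ (1 to 3) or ‘Absent’ (0) ranges".
- MASC: "this will be a shift in t-score between the ‘Severe’ (≥70); ‘Moderate’ (56 to 69) and ‘Non-clinical’ (≤55) ranges".
- CBCL: "a change in t-scores among the ‘Clinical’ (≥69); ‘Borderline clinical’ (56 to 69) and ‘Normal’ (≤55) ranges".

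Reliability is described only in words. The MASC is said to have "moderate-to-strong internal reliability, and adequate test-retest and discriminate validity"; for the CBCL, validity and reliability "were found to be moderate-to-high and high, respectively". The Statistical analysis section plans paired t-tests and linear mixed models for pre versus post change in primary and secondary outcomes. It names no test for the proportion of participants who change band.

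**The concern.** The rule asks only which side of a cut-point a score lies on. It can therefore rank a trivial change above a large one, and it counts movement that repeat measurement would produce without any real change. Because it speaks of a change or a shift, a worsening also meets it as written.

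This is a complete rule, with its cut-points, for a primary outcome; it is not a detail left to another document. Two things are at stake. First, the proportion carrying the label will contain noise in all three arms, so neither its absolute level nor a within-arm reading can be taken at face value. Second, the noise shrinks differences between arms. That matters when one hypothesis is that ACT does at least as well as CBT, because a diluted contrast looks reassuring.

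**Working it through.** **Step 1. What follows from the printed cut-points, with no assumptions.**

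- MASC 56 to 55 and 70 to 69 are one-point changes that cross a band: counted.
- MASC 69 to 56 is a 13-point fall (69 − 56 = 13) within the Moderate range: not counted. MASC 85 to 70 stays in the open-ended top range: not counted.
- On the ADIS-IV, 4 of the 8 possible one-point improvements count (8 to 7, 6 to 5, 4 to 3, 1 to 0). The two-point improvement from 3 to 1 does not.
- On the CBCL, 69 lies in both the Clinical and the Borderline range, so 69 to 56 is ambiguous. The unambiguous in-band fall is 68 to 56, 12 points.

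**Step 2. Band crossings from error alone (MASC bands).** The article gives no rate to reproduce. Assumed inputs: T-score SD 10, baseline mean 60 to 70, reliability r of 0.7 to 0.9, no true change. Model: observed score = true score + error, with error SD = SD × √(1 − r), rounded to whole points. One million simulated participants per setting:

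| r | Mean | Lower band | Different band, either way | Lower band and beyond the reliable-change limit |
|---|---|---|---|---|
| 0.7 | 60 / 65 / 70 | 18.8% / 18.7% / 16.5% | 37.6% / 37.5% / 33.0% | 2.1% / 2.1% / 1.9% |
| 0.8 | 60 / 65 / 70 | 15.4% / 15.5% / 13.6% | 31.0% / 31.0% / 27.2% | 2.0% / 2.0% / 1.8% |
| 0.9 | 60 / 65 / 70 | 11.0% / 11.1% / 9.6% | 22.0% / 22.0% / 19.3% | 1.8% / 1.8% / 1.6% |

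The reliable-change limit is 1.96 × SD × √(2(1 − r)):

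- r = 0.7: 1.96 × 10 × √0.6 = 15.2 points
- r = 0.8: 1.96 × 10 × √0.4 = 12.4 points
- r = 0.9: 1.96 × 10 × √0.2 = 8.8 points

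**Step 3. Wider assumptions.** With means 55 to 70, SD 8 to 12 and r 0.7 to 0.95, crossings to a lower band are about 6% to 20%, and in either direction about 12% to 40%. For the ADIS-IV, with separate assumptions (baseline rating at least 4, mean 5.5 to 6.5, SD 1 to 1.5, r 0.7 to 0.9), downward crossings are 9% to 24%.

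**Step 4. Band outcome against continuous score as the tested quantity.** Assumptions: true mean fall of 6 points in one arm and 0 in the other, individual SD of true change 5 in both arms, 50 per arm (150 / 3, both age groups together, no drop-out), two-sided 5% test.

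- Continuous change score: variance per arm = 5² + 2 × 10² × (1 − r). At r = 0.7 this is 85, the standard error is √(2 × 85 / 50) = 1.84, and power = Φ(6/1.84 − 1.96) = 0.90. At r = 0.9 the variance is 45, the standard error 1.34 and power 0.99.
- Downward band crossing: power = Φ(|p₁ − p₂| / √((p₁(1 − p₁) + p₂(1 − p₂))/50) − 1.96). The lowest case (mean 60, r = 0.7) has 20.9% against 37.4%, power 0.46. The highest (mean 70, r = 0.9) has 15.2% against 38.0%, power 0.76.

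**Step 5. What a reliable-change limit does to large gains.** With a true mean fall of 6 to 8 points (individual SD 5), the share of observed improvements of 10 or more points left uncounted is:

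| r | Band only | Band and limit |
|---|---|---|
| 0.7 | 17–26% | 56–64% |
| 0.8 | 19–29% | 41–51% |
| 0.9 | 22–33% | 22–33% |

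These shares include participants who start at 55 or below and cannot move down. Among those starting at 56 or above, with a mean fall of 7, the band-only share is about 6% to 18%.

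**The case against.** The strongest reply has four parts.

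- The bands are fixed in advance and attributed to cited sources, and every categorical outcome has edges. This is true, but it does not supply a minimum change or a direction.
- The planned linear mixed models suit continuous scores, and no test of responder proportions is named. This stands. The remedy is therefore mainly a clarification, and the power comparison concerns a yes/no test that the article does not specify.
- Post-treatment and follow-up interviews are re-rated by an independent assessor. That bears on ADIS-IV rater error, but not on the MASC or CBCL.
- A stricter rule has its own cost. This also stands: Step 5 shows that requiring both a lower band and a reliable fall leaves more large gains uncounted at reliability 0.7 to 0.8, so it should not become the sole definition.

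Three stronger readings are tempting and are not supported. A reader might take 10% to 19% as a known rate for every scale; it depends on assumed inputs and was computed for MASC bands. A reader might infer a false difference between arms; error unrelated to arm does not create one by itself. A reader might infer that worsening will be scored as treatment success; the article does not say so, and only leaves the direction unstated.

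**Conclusion.** The point holds as a defect in how a primary outcome is fixed. That one-point crossings count and a 13-point MASC fall does not is certain from the printed ranges. The size is conditional: about 10% to 19% of participants moved to a lower MASC band by error alone, and 19% to 38% to a different band, at SD 10, mean 60 to 70 and reliability 0.7 to 0.9; about 6% to 20% downward over the wider grid. The consequences are inflated absolute and within-arm rates and diluted contrasts. The change is worth making before analysis.

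**What to change.** 1. State that the between-arm efficacy tests on ADIS-IV severity, MASC and CBCL use the continuous scores in the linear mixed models already planned.
2. Define the band outcome as improvement, meaning a move to a lower range, and reconcile the CBCL ranges at 69 so that each score has one range.
3. Report that proportion by arm descriptively. Beside it, report the stricter proportion that also exceeds 1.96 × SD × √(2(1 − r)), with SD and r for each scale fixed in advance and their source given.

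The cost is wording and one computed variable per scale; no new method is needed. The downside is that the stricter proportion shows fewer responders and, at reliability 0.7 to 0.8, omits more large observed gains. It should accompany the band proportion, not replace it as a tested endpoint.
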